## Abstract

**Background:**

Due to some unique physical, social and psychological features in the adolescent population, adolescents can be a time of heightened caries activity and periodontal disease. Oral health-related behaviors can be modified to improve oral health status. The family networks and the built environment can promote or inhibit health behaviors. The aim of this study is to implement and evaluate a behavior theory-based, integrated family intervention via mobile messaging to improve oral health of adolescents.

**Methods:**

This is a three-arm parallel-design cluster-randomized controlled trial. This trial will allocate 12 local secondary schools (clusters) in Hong Kong to three test or comparison groups with a ratio 1:1:1. The enrolled Form II to IV students (ages 12 to 15) will be eligible for participation. The intervention to three study groups will be (i) Health Belief Model (HBM)-based mobile messaging to the adolescents and their parents, which will consist of several blocks of HBM-based messages and reinforcement during 24 weeks; (ii) same HBM-based messaging to adolescents only; and (iii) delivering e-version of oral health education pamphlets to adolescents. The primary outcome will be caries increment 2 years post-intervention. Changes in oral health self-efficacy and behaviors, oral hygiene, and gingival status will be the secondary outcomes.

**Discussion:**

No school dental care service is available to secondary school students in Hong Kong. This study will be the first to test a theory-driven and family-engaged preventive intervention among adolescents in Hong Kong. Findings will contribute to developing a low-cost, feasible, and efficient oral health preventive program for adolescents.

**Trial registration:**

ClinicalTrials.govNCT05448664. Registered on 7 July 2022.

## Administrative information

Note: the numbers in curly brackets in this protocol refer to SPIRIT checklist item numbers. The order of the items has been modified to group similar items (see http://www.equator-network.org/reporting-guidelines/spirit-2013-statement-defining-standard-protocol-items-for-clinical-trials/).

## Introduction

### Background and rationale {6a}

Adolescents are very broadly defined as youths between the ages of 10 to 19 [1]. Due to some unique physical, social and psychological features in the adolescent population, adolescence can be a time of heightened caries activity and periodontal disease due to an increased intake of cariogenic substances (e.g., consumption of high quantities of refined carbohydrates and sugar-containing beverages) and inattentive to proper oral hygiene procedures due to a low priority [2].

As dental caries and periodontal disease are highly determined by one’s “lifestyle” and are preventable, primary prevention by addressing risk and protective factors and improving oral health behaviors is key to reversing the unhealthy trends. Since adolescents is a critical transitional stage to adopt positive health habits, efficient interventions at this age are essential for preventing oral diseases over a lifetime.

Traditional oral health education (OHE) focuses on solely the dissemination of information and normative advice, which may not result in changes in the recipients’ behaviors [3]. Over the years, behavior theory-driven approaches have been developed and demonstrated potential in improving oral health knowledge, attitudes and behaviors, and caries prevention in adolescents [4]. Health Belief Model (HBM) has been recommended as a useful theoretical model to explain and promote healthy behaviors [5]. HBM suggests that health-promoting behaviors can be triggered by six domains: perceived susceptibility, perceived severity, perceived barriers, perceived benefit, cue to action, and perceived self-efficacy. HBM-based intervention, to some degree, has been introduced to the field of dentistry. Some studies indicated that face-to-face HBM-based education has a significant effect in improving oral health behavior for school children and adolescents [6, 7].

Nevertheless, face-to-face HBM-based intervention can be resource-intensive and challenging to implement at the population level. It may require participants’ frequent on-site participation which could bring to low adherence and high dropout rates. A more convenient, accessible, and time-efficient approach is needed and preferred. Mobile health (mHealth) is a rapidly expanding field in the digital health sector, providing healthcare support, delivery, and intervention via mobile technologies such as smartphones, tablets, and wearables. A key benefit of mHealth is that it has the potential to deliver personalized, interactive, and adaptive health interventions in the context of an individual’s everyday life. It could overcome the traditional barriers faced by healthcare practitioners (such as time and resource constraints), especially among the hard-to-reach populations [8]. To date, there is some evidence that behavior theory-based oral health promotion utilizing mobile messaging app was effective in improving oral hygiene among adolescents with fixed orthodontic appliances [9, 10]. Whereas the use of social media-based applications alone, without a behavior theory-based model, failed to change oral hygiene behavior [11].

It has been reported family network and the built environment may work together to promote or inhibit lifestyle behaviors. Parents have a central role in educating their children and encouraging and supporting their healthy lifestyle choices [12]. Current concepts of oral health education acknowledge the importance of involvement at individual, family, and even community levels [4, 13]. However, studies on how behavior theory-based intervention can be used in the family network and the built environment to improve adolescent oral health are very rare.

To sum up, inspired by HBM combined with a family network approach and using mobile technology as a vehicle, a viable oral health promotion model will be explored and tested in this study. Its effectiveness in promoting the oral health of adolescents will be evaluated in a randomized controlled trial setting.

### Objectives {7}

The objective of this study is to investigate the effectiveness of the family- and HBM-based mobile-health behavioral intervention in enhancing adolescents’ good oral health behaviors (mainly oral hygiene practice and free sugar intake control) and preventing common oral diseases (dental caries and periodontal diseases).

The research hypothesis is the proposed family- and HBM-based mobile-health behavioral intervention is more effective than intervention on the adolescents alone or prevailing OHE in improving the adolescents’ behaviors and oral health.

### Trial design {8}

This study is a three-arm parallel design, superiority, cluster-randomized controlled trial comparing three interventions. Interventions will be applied at the cluster (school) level. Either active or comparator intervention is administered to the school by randomization to prevent contamination. The allocation ratio is 1:1:1.

## Methods: participants, interventions, and outcomes

### Study setting {9}

This study will be carried out in 12 secondary schools in Hong Kong, the primary sampling unit, and formed the clusters of the trial. A list of secondary schools will be obtained from Hong Kong Education Bureau (https://www.edb.gov.hk/en/student-parents/sch-info/sch-search/schlist-bydistrict/index.html). To balance the social-economic status, 3 local co-educational public or government-subsidized schools from Hong Kong Island, 6 from Kowloon, and 3 from New Territories will be selected and randomly allocated to the 3 groups within each geographical region of Hong Kong.

### Eligibility criteria {10}

The target population will be adolescents aged 12 to 15 years old (Form II to Form IV students) and their parents or primary caregivers. The Form-I students will not be invited because they attended the School Dental Care Services provided to primary school students by the Department of Health less than one year ago.

Inclusion criteria are as follows: (i) Chinese ethnicity; (ii) student living with their parent(s) or primary caregiver(s); and (iii) both student and parent(s) or primary caregiver having their access to a personal mobile phone with certain Apps to receive the messages in time (e.g., WhatsApp or WeChat).

Exclusion criteria are as follows: (i) student currently on a special diet (e.g., severe inflammatory bowel disease); (ii) student has medical conditions known to affect growth or eating (e.g., diabetes, cystic fibrosis); and (iii) enrollment in other oral health promotion programs or research studies.

### Who will take informed consent? {26a}

The participating secondary schools will help to invite students and their parents/caregivers. One class in each Form II to Form IV student will be approached. The information sheet and consent form will be distributed to the students and their parents via school. The parent/caregiver and the research investigator will sign the informed consent.

### Additional consent provisions for collection and use of participant data and biological specimens {26b}

An ancillary study that uses participants’ dental plaque and/or saliva to explore the oral microbiome composition will be proposed for selected participants. Additional consent will be provided for the collection and use of participant biological data.

### Explanation for the choice of comparators {6b}

This study adopts two active control groups to verify the effectiveness of the behavioral theory-based family intervention via mobile messaging for oral health promotion. One of the active control groups will receive similar mobile messages as the test group does not include their parents. The other active control group will receive the e-version of OHE pamphlets published by the government, which could be considered the prevailing OHE.

### Intervention description {11a}

#### Group (i) family- and HBM-based behavioral intervention via mobile messaging

The mobile messages based on the HBM model will be sent to the students and their parents in two stages over 24 weeks.

##### Stage I — HBM message series

During the 1st week to the 12th week, text messages exchanged with participants will be organized into six domains guided by HBM [14]. Each domain will comprise various topics and types of messages, e.g., text, photos, or animation demonstration on toothbrushing and flossing. All the messages will be developed using evidence-based content from previous research findings. First, the students and their parents must have some basic knowledge of dental caries and periodontal diseases so that they can be motivated toward a healthy dentition for adolescents (perceived susceptibility). Second, they must perceive that adolescents with poor oral health care and highly sugary diet are at increased risk for oral disease and that poor oral health could also affect general health (perceived severity). Third, the students and parents must also be convinced that regular toothbrushing and control of sugar intake for their children are effective to prevent oral diseases (perceived benefits). Fourth, the students and their parents will identify the barriers to daily oral hygiene practice and added-sugar intake control (perceived barriers). Fifth, the presence of an internal or external stimulus, referred to as “cue to action,” triggers the student’s self-oral health care behavior and promotes the parents to involve, support, and monitor the daily oral health behavior of their children. The toothbrushing and sugar intake control reminders and tips will be designed to support behavior change (e.g., “Time to brush your teeth.” and “Remember to bring along your water bottle so you possibly will not go for a sweet beverage after sporting.”). Finally, empower the student’s self-efficacy through the interaction between researchers and his/her family (perceived self-efficacy). On average, participants are expected to receive a series of 3–5 messages every week during these 12 weeks.

The parents will also receive the mobile message to improve the family’s healthy lifestyle choices except for the knowledge regarding adolescent oral health. For example, “Please use tap water for cooking” (tap water in Hong Kong contains 0.5 ppm fluoride and is a benefit for caries prevention) and “Please don’t prepare too many sugar-added snacks for your child.” The parents will also receive reminder messages to observe, supervise and encourage their child’s proper oral health behavior (e.g., “Do you know your child is brushing his/her teeth properly?” etc.).

##### Stage II — feedback and reinforcement

From the 13th week onwards, we will ask the students and their parents about students’ self-efficacy and collect self-reported information on adherence. For example, we will ask the students “How many of the past seven days have you brushed your teeth twice daily?” and “How many of the last seven days have you taken sweet-beverage more than twice daily?”). Messages of assessment and feedback (e.g., “Great job!”) will be feedback to the students and their parents. The participants will expect to receive 1–2 messages every week over these 12 weeks.

#### Group (ii) HBM-based behavioral intervention via mobile messaging to adolescents

Text messaging based on the HBM model and reinforcement same in group (i) will be delivered to the participating students over 24 weeks. The parents will not receive the intervention.

#### Group (iii) Delivering e-version of oral health education pamphlets to adolescents

The e-version of three pamphlets, namely “*Cleaning teeth properly – You can do it*,” “*How to use dental floss*,” and “*Healthy diet, healthy teeth*” published by the Department of Health, Hong Kong SAR (http://www.toothclub.gov.hk/en/en_index.html) will be delivered separately via mobile messaging.

## Criteria for discontinuing or modifying allocated interventions {11b}

Enrollment is voluntary. The participants can withdraw from the study at any time after enrolment without giving any reason. The statement will be clearly stated in the information sheet to the students and their parents before obtaining their consent. The intervention in this study is mobile messaging, with no harm to participant health.

## Strategies to improve adherence to interventions {11c}

To check compliance with the intervention, we will communicate with the participants in the intervention groups every three months through messaging or a short online questionnaire. The pre-set questions of Goal Attainment Scaling (GAS) will be sent to the participants to check their compliance with the intervention [15]. The participants will self-assess their behavioral goal attainment of expected outcomes. It enables a linkage of reports and measures from the participants to upper levels of project management.

## Relevant concomitant care permitted or prohibited during the trial {11d}

During the trial, all the participants will not prohibit from dental visits for check-ups or treatments. The specific category of the dental visit will be asked for and recorded in each follow-up (e.g, dental fillings, teeth cleaning, and orthodontic treatment).

## Provisions for post-trial care {30}

We will provide dental examination reports to the participants, and suggest dental visits when dental problems are found during the trial. There is no additional post-trial dental care for all participants.

## Outcomes {12}

The primary outcome will be dental caries increment (by tooth level). The students will be examined at the schools at baseline, 1-year, and 2-year follow-up. Dental caries assessment will base on the ICDAS criteria (International Caries Detection and Assessment System), which will be used to assess both non-cavitated (codes 1 and 2) and cavitated caries lesions (codes 3–6) [16]. The examiners will examine occlusal, mesial, distal, buccal, and lingual surfaces of each tooth.

The secondary outcomes will be:i)Gingival status measured by the percentage of sites with gingival bleeding (BOP%), as recommended by the WHO for conducting oral health surveys [1];ii)Oral hygiene status using the Visible Plaque Index (VPI). The percentage of plaque on the buccal and lingual surfaces of all indicated teeth will be recorded [1];iii)Average frequency of toothbrushing per day (2 times as preferred);iv)Average frequency of intake of sugary snacks/drinks per day (2 times or less frequent as preferred);v)Average amounts of free-sugar intake per day (<25 g as preferred); andvi)Oral health self-efficacy on behaviors (questionnaire score rated on a 4-point Likert scale, e.g., 1 = not confident at all to 4 = very confident)

## Participant timeline {13}

The participant timeline is shown in Fig. 1. The schematic diagram template was downloaded from http://www.spirit-statement.org/publications-downloads/.

**Fig. 1 Fig1:**
[figure not shown]
Schedule of enrolment, interventions, and assessments

## Sample size {14}

The sample size has been calculated using G*Power software. Our previous study showed that motivational interviewing was more effective than prevailing OHE in preventing dental caries among adolescents [17]. In this proposed study, the sample size is calculated based on mean and standard deviations of the primary outcome measure — the number of new carious teeth (∆DMFT). From the pre-existing study, an effect size of 0.21 was obtained for tooth status over 24-month evaluation (∆DMFT: test group=0.12 vs. control group=0.34; SD ~ 0.50) [18], which could be considered a moderate size convention for 1-way ANOVA and clinically significant for the primary outcome [19]. Based on a significance level of 5% and a targeted statistical power of 80%, 74 participants in each group will be required. Considering a typical value of ICC = 0.03 in a cluster randomized clinical trial setting [20] and if 75 children are to be recruited from each school, the design effect will be 3.22 [21]. Assuming a similar dropout rate as our previous study in secondary school at the 2-year follow-up (dropout rate: 10%) [17], the sample size will be increased to 300 in each group, thus 900 altogether. Then 4 schools in each group, a total of 12 schools will be recruited.

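### The sample size makes no allowance for having only 12 randomised schools: on the plan's own inputs, power is about 74% (69% if region is fitted and explains nothing), not 80%

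*Protocol article*

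**What the plan says.** Under Sample size {14}, the trial is sized in G*Power on the two-year increment in DMFT. The plan reports that "an effect size of 0.21 was obtained for tooth status over 24-month evaluation", from means of "test group=0.12 vs. control group=0.34" and an SD of about 0.50, and it adds "which could be considered a moderate size convention for 1-way ANOVA". The first result is: "Based on a significance level of 5% and a targeted statistical power of 80%, 74 participants in each group will be required".

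Clustering comes in next: "Considering a typical value of ICC = 0.03 in a cluster randomized clinical trial setting", with 75 children per school, gives a design effect of 3.22. After 10% dropout the plan arrives at 300 per group and 900 in all. It ends: "Then 4 schools in each group, a total of 12 schools will be recruited".

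Other sections fix the structure of the comparison:
- Trial design {8} applies the interventions to whole schools, and "The allocation ratio is 1:1:1".
- Study setting {9} allocates schools within three regions containing 3, 6 and 3 schools.
- Statistical methods {20a} fits school as the top level of a three-level random-intercept model. The only covariates it names are gender and parental education.

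**The concern.** The school is the unit of randomisation, so the arms are compared against the variation between schools. The information about that variation comes from 12 schools, not from several hundred students. Two separate adjustments are needed when an individual-level calculation is carried over to such a design. One enlarges the variance, which the design effect does. The other replaces the individual-level error df with those that the schools provide, which the plan does not do. With four schools per arm the second adjustment is large, because the critical value of the F test rises from about 3.04 to 4.26 or more.

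At stake is how a null result would be read. A trial described as having 80% power would, on its own assumptions, have roughly a 26% to 31% chance of missing its target effect instead of 20%.

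**Working it through.** **Inputs.** From Sample size {14}: f = 0.21, two-sided alpha 0.05, ICC 0.03, 75 students per school, 10% dropout, 4 schools per arm, means 0.12 and 0.34, SD 0.50. From Study setting {9}: three regional strata.

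**Step 1: reproduce the plan.**
- Three-group ANOVA with 74 per group: N = 222, error df = 222 − 3 = 219, noncentrality = 222 × 0.21² = 9.79, critical F(2, 219) = 3.04. Power is 80.1%, so 74 is confirmed.
- Design effect: 1 + (75 − 1) × 0.03 = 3.22.
- 74 × 3.22 = 238.3, and 238.3 / 0.9 = 264.8, so 265 per arm. The plan goes up to 4 × 75 = 300.

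**Step 2: information at the two-year analysis.**
- Analysed per school: 75 × 0.9 = 67.5, or 270 per arm.
- Design effect at that size: 1 + 66.5 × 0.03 = 2.995.
- Effective n per arm: 270 / 2.995 = 90.2.
- Noncentrality: 3 × 90.15 × 0.21² = 11.93.

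**Step 3: df for comparing arms.**
- 12 schools − 3 arms = 9.
- With region fitted (two further parameters): 9 − 2 = 7.
- Gender and parental education vary between students and use no school-level df.

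**Step 4: power from the noncentral F distribution with noncentrality 11.93.**

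| Error df | Critical F | Power |
|---|---|---|
| Individual-level | about 3.03 | 87.7% |
| 9 (schools, region not fitted) | 4.26 | 74.0% |
| 7 (schools, region fitted, no variance gain) | 4.74 | 69.3% |

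Going from 265 to 300 lifts the nominal power to 87.7%. Using school-level df then takes off about 14 points (9 df) or 18 points (7 df), which leaves 6 or 11 points short of the target.

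**Step 5: sensitivity to the ICC** (67.5 analysed per school, f = 0.21; effective n per arm = 270 / design effect).

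| ICC | Design effect | Effective n per arm | Power, 9 df | Power, 7 df |
|---|---|---|---|---|
| 0.02 | 2.33 | 115.9 | 84% | 80% |
| 0.03 (plan) | 2.995 | 90.2 | 74% | 69% |
| 0.05 | 4.325 | 62.4 | 57% | 53% |

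Power reaches 80% at an ICC of about 0.024 (9 df) or 0.020 (7 df).

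**Step 6: the plan's pairwise contrast.**
- Difference: 0.34 − 0.12 = 0.22. Standard error: 0.50 × √(2 / 90.15) = 0.0745. Ratio: 2.95.
- Noncentral t power at unadjusted alpha 0.05: 74.8% (9 df) or 71.8% (7 df).
- Difference detectable with 80% power: 0.235 (9 df) or 0.244 (7 df).

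**The case against.** The strongest reply is that nothing in the section is miscalculated, and that stands. The 74, the 3.22 and the step to 300 all hold. A reader might infer an arithmetic error, but the problem is an allowance that was left out.

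Second, 69% should not be read as the plan's own power. Study setting {9} randomises within region, but Statistical methods {20a} does not list region in the model, so the analysis as written leaves 9 df and 74%. The 7-df figure also charges two df for region and credits nothing in return, although the regions were chosen to balance socio-economic status. If region removed 20% or 30% of the between-school variance (an assumption; the document gives no figure), 7-df power would be about 76% or 79%. So 69% is the case in which stratification gains nothing. Figures of 66% to 71% can also be produced by keeping the design effect of 3.22 after dropout, but that pairs a full-enrolment cluster size with a post-dropout sample and understates power.

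Third, the ICC is described only as a typical value. At 0.02 the design meets its target even with 7 df. That is a reason to show a range. It does not rescue the stated power at the 0.03 that the plan adopted.

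Fourth, a reader might infer that the planned tests have inflated type I error because there are few schools. The document does not support this. The models include school as a random level, and no reference distribution or df method is stated. That detail can properly sit in a statistical analysis plan that is not shown.

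A last argument, that the repeated visits add df, does not help. Treatment varies only between schools, so further visits create no further randomised units.

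**Conclusion.** The concern holds as a shortfall in the sample-size justification. On the plan's own effect size, ICC, cluster size and dropout, 12 schools give about 74% power for the three-group comparison. That is 6 points below target. The figure is about 69% if region is fitted and explains no between-school variance. The planned pairwise contrast leads to the same conclusion.

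The result rests on equal cluster sizes, on the plan's ICC of 0.03, and on no credit for variance removed by stratification or covariates, none of which the document quantifies. At an ICC of about 0.02 the shortfall disappears; at 0.05 power falls to between 53% and 57%. Nothing here shows a biased estimate or an invalid test.

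**What to change.** In Sample size {14}, keep the existing steps and add a restatement based on school-level df:
- power of about 74% at ICC 0.03, or 69% with region fitted and no variance gain;
- the ICC range: about 84% or 80% at 0.02, and 57% or 53% at 0.05;
- the pairwise difference detectable with 80% power, about 0.235 to 0.244 DMFT, in place of 0.22.

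As a recommendation that matches the restated power, and not as the correction of an error in Statistical methods {20a}, use small-sample df (Satterthwaite or Kenward-Roger) when arms are compared in the school-level models.

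The cost is a few sentences and a less favourable stated power. No school or student needs to be added to make this correction.
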